# Intervention for Sleep and Pain in Youth (ISPY-RCT): protocol for a two-phase randomized controlled trial of sequenced cognitive-behavioral therapy for insomnia and pain management in adolescents with migraine

**DOI:** 10.1186/s13063-022-07035-9

**Published:** 2023-01-12

**Keywords:** Digital health, Internet interventions, Migraine, Headache, Insomnia, Sleep, Child, Adolescent, Pediatric, Cognitive behavioral therapy

## Abstract

**Background:**

Migraine is a major pediatric health problem impacting 10–12% of youth. About 1 in 3 youth with migraine are diagnosed with insomnia. Sleep and migraine share a cyclical relationship, and data indicate that insomnia symptoms increase migraine severity. CBT for insomnia (CBT-I) has demonstrated efficacy for improving insomnia in adults with migraine and other pain conditions; however, effects in youth have not been evaluated. Moreover, in adults, there is some indication that CBT-I may lead to changes in pain after there are sustained improvements in sleep, but this has never been empirically tested. Cognitive-behavioral therapy for pain management (CBT-Pain) is an established treatment approach for youth with migraine, leading to reductions in headache frequency and disability. In the proposed study, we will address these gaps in knowledge by using an innovative two-phase trial design to (1) test the efficacy of Internet-delivered CBT-I intervention for youth with migraine and comorbid insomnia compared to Internet-delivered sleep education for modifying sleep and (2) investigate how changes in sleep may modify the response to Internet-delivered CBT-Pain intervention.

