### Outcomes {12}

The primary outcome following treatment phase 1 is change in self-reported insomnia symptoms (Insomnia Severity Index (ISI) [27]) from pre-randomization/baseline to immediately after treatment phase 1, immediately after treatment phase 2, and 6-month follow-up. The ISI has shown strong validity and reliability estimates, including sensitivity to change in response to insomnia treatment for teens with physical and mental health comorbidities [14, 15]. Secondary outcome measures of sleep include self-reported sleep quality (Adolescent Sleep-Wake Scale-Short Form (ASWS-SF)) [28] and sleep patterns (sleep duration, sleep efficiency, and wake after sleep onset) assessed using 14 days of daily sleep diary and actigraphic monitoring (Actiwatch Spectrum Plus, Phillips Respironics, Bend, OR) [29, 30].

The primary outcome following treatment phase 2 is change in activity limitations due to headache (Child Activity Limitations Interview-9 (CALI-9)) [31] from baseline to phase 1 post-treatment, phase 2 post-treatment, and 6-month follow-up. The CALI-9 measures difficulty in performing usual daily physical, social, and recreational activities (e.g., going to school, participating in activities at home) due to headache and has demonstrated sensitivity to change in response to CBT-pain treatment. Adolescents will complete a 14-day electronic diary which includes (1) the CALI-9 diary version [32], (2) the presence of headache (yes/no) to compute headache frequency [33] (secondary outcome), and (3) headache pain intensity (11-point Numerical Rating Scale (NRS)) [34] (secondary outcome). Additional secondary outcomes include self-reported emotional functioning (PROMIS Pediatric Anxiety and Depression short form scales v.2.0) [32] and health-related quality of life (youth self-report Pediatric Quality of Life Inventory 4.0) [35].

Adolescents and parents will complete a Treatment Experience Survey adapted for this study [36] concerning whether they experienced negative effects of study participation (e.g., worrying about sleep or pain, overwhelmed with treatment assignments, tension at home) and rate the level of discomfort experienced (0 = did not affect me/my teen at all, 3 = affected me/my teen very negatively). The number, type, and severity of negative experiences will be summarized. Participants will also report adverse events via free text response at each assessment time point.

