## Statistical methods

### Statistical methods for primary and secondary outcomes {20a}

Given the 2-phase RCT design, group comparisons for sleep outcomes will be assessed at phase 1 post-treatment. We will compare insomnia symptoms (primary outcome), sleep quality, and sleep patterns and their corresponding changes from baseline to phase 1 post-treatment between CBT-I and Sleep EDU using the Student *t*-tests or chi-squared tests. Baseline demographic and pre-treatment variables are expected to be balanced across treatment conditions by randomization but will be checked. We will conduct covariate-adjusted regression analysis on the outcomes: linear regression models on continuous outcomes and logistic regression models on binary outcomes, with a priori identified biological covariates (age, sex), sociodemographic variables (race, ethnicity), and baseline outcome values. The predictor of interest is the treatment condition indicator. All regression models will be carefully assessed using residual analysis and goodness-of-fit statistics (deviance, likelihood ratio, information criteria, etc.). The primary hypotheses will be tested using the Wald test on the coefficient estimates of treatment condition indicator.

Group comparisons for headache outcomes and emotional and health outcomes will be assessed at phase 2 post-treatment and 6-month follow-up. Similar analyses as outlined for phase 1 outcomes above will be applied for cross-sectional analyses of post-treatment phase 2 outcomes. Longitudinal data analysis will examine the sleep and headache outcome variables assessed at all 4 time points (baseline, phase 1 post-treatment, phase 2 post-treatment, 6-month follow-up). All regression models will have the following form: outcome ~ group + time + time × group + confounders. We will model time as a discrete variable. The differences in changes from baseline in outcomes between the treatment groups will be assessed by testing the significance of coefficients for the time-by-group interaction terms using the Wald test (individual) and likelihood ratio test (overall). To account for clustering due to repeated assessments within individuals, we will use linear and generalized linear mixed effects regression models.

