## Discussion

This randomized controlled trial is designed to investigate the efficacy of Internet-delivered CBT-I compared to Internet-delivered Sleep EDU in 180 adolescents with migraine and insomnia. The potential synergistic effects of delivering CBT-I followed by CBT-Pain on headache outcomes and emotional and health outcomes will also be examined by comparing CBT-I+CBT-Pain to Sleep EDU+CBT-Pain.

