### Limitations

There are several limitations to consider. First, the study protocol may be time intensive which might impair enrolment or increase drop-out. The risk of drop-out will be minimized by informing potential participants of the study protocol during the recruitment and enrolment process. Second, the comparison of CBT-I to Sleep EDU is limited to the immediate phase 1 post-treatment assessment at phase 1, and subsequent assessment time points will reflect the addition of CBT-Pain to either CBT-I or Sleep EDU. We chose the 2-phase trial design to provide information about the potential synergistic effects of sleep and pain interventions. Finally, this is a single-site study of youth recruited from a tertiary care pediatric neurology clinic. Our findings may not generalize to patients seen in other settings.

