### Strengths

The results of this study will provide the first rigorous RCT data on the treatment of comorbid migraine and insomnia in adolescents. Furthermore, the innovative 2-phase design allows for testing the impact of insomnia intervention compared to control in the first phase while then allowing a comparison of insomnia and pain intervention to pain intervention alone in the second phase. These data are critical for understanding the potential limitations (or benefits) of CBT-Pain interventions in youth with migraine and comorbid sleep problems can help determine whether CBT-I intervention has the potential to improve response to CBT-Pain treatment in this population and can further our conceptual understanding of the sleep-pain relationship.

Using the Internet to deliver treatment is also a strength by providing a scalable intervention that has the potential to be widely disseminated. Because the development and evaluation of insomnia interventions in pediatrics have lagged far behind adult therapies, we developed the Firefly intervention as a stand-alone intervention for insomnia. This provides a future opportunity to extend the Firefly program to a wide spectrum of youth with insomnia, such as those with other health or mental health conditions (e.g., cancer, arthritis, major depression) who are also at high risk for comorbid insomnia.

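### The phase 2 comparison validly tests the combined sequence, but by itself cannot show synergy or a changed response to CBT-Pain

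*Protocol article*

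**What the plan says.** The protocol article describes the phase 2 question in two ways.

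- **Superiority of a sequence.** Objectives {7} and Trial design {8} ask whether CBT-I followed by CBT-Pain is better than Sleep EDU followed by CBT-Pain, with headache-related disability (CALI-9) as primary outcome.
- **Modification or synergy.** The abstract wants to "investigate how changes in sleep may modify the response to Internet-delivered CBT-Pain intervention". The Discussion speaks of "The potential synergistic effects of delivering CBT-I followed by CBT-Pain on headache outcomes", which "will also be examined by comparing CBT-I+CBT-Pain to Sleep EDU+CBT-Pain". Limitations says: "We chose the 2-phase trial design to provide information about the potential synergistic effects of sleep and pain interventions". Strengths says the data "can help determine whether CBT-I intervention has the potential to improve response to CBT-Pain treatment in this population".

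The stated analyses are in Statistical methods {20a}. One is an arm comparison at phase 2 post-treatment, using t-tests and regression adjusted for the baseline value. The other is a mixed model over all four time points with discrete time, of the form "outcome ~ group + time + time × group + confounders". Its time-by-group terms are read as follows: "The differences in changes from baseline in outcomes between the treatment groups will be assessed by testing the significance of coefficients". Outcomes {12} likewise defines CALI-9 change from baseline, at each of the three later assessments.

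Background {6a} proposes that treating insomnia could itself help headache, and reports that the team's in-person CBT-I improved headache disability and frequency. Every participant receives CBT-Pain in phase 2.

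**The concern.** A response to CBT-Pain is what happens to headache while CBT-Pain is given. The planned phase 2 comparison starts its clock at baseline, before CBT-I. If CBT-I lowers CALI-9 during phase 1 and the gain lasts, the arms will differ at phase 2 even when both respond to CBT-Pain identically.

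The Discussion nevertheless names this comparison as the way synergy will be examined. At stake is the reading of a positive result: a simply additive benefit of CBT-I could be taken as evidence that better sleep makes CBT-Pain work better. That would bear on whether CBT-I needs to come before CBT-Pain or is merely useful in its own right.

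**Working it through.** **The plan's own figure.** For 80% power at d = 0.45 with two-sided alpha 0.05 (alpha is not stated, so this is assumed): n = 2 × (1.960 + 0.842)² / 0.45² = 77.5, or 78 per arm against the stated 77. Power at 77 per arm is 79.7%. The figure reproduces.

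**What the planned contrast estimates.** Let T0, T1 and T2 be baseline, phase 1 post-treatment and phase 2 post-treatment. Let D1 be the arm difference in CALI-9 change from T0 to T1, and D2 the arm difference in change from T1 to T2.

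- Time-by-group coefficient at T1 = D1.
- Time-by-group coefficient at T2 = D1 + D2.
- Difference of the two coefficients = D2.

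Only D2 concerns the CBT-Pain period. The phase 2 test is of D1 + D2. Adjusting for baseline does not remove D1, because D1 arises after baseline.

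**How often an additive effect alone gives significance.** Inputs: 77 per arm (Sample size {14}). Assumed: SD 1 at each time, equal within-person correlation r, alpha 0.05 two-sided, direct effect δ present at T1 and fully kept at T2, D2 = 0.

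For change scores, SE = √[2 × 2(1 − r) / 77], which is 0.161 at r = 0.5 and 0.125 at r = 0.7. Power ≈ Φ(δ/SE − 1.96). The table sets this beside 4,000 simulated trials per row with t-tests on change scores.

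| r | Direct effect δ | T2 − T0, formula | T2 − T0, simulated | T2 − T1, simulated |
|---|---|---|---|---|
| 0.5 | 0.20 | 24% | 23% | 5.0% |
| 0.5 | 0.30 | 46% | 46% | 5.4% |
| 0.5 | 0.45 | 80% | 78% | 5.0% |
| 0.7 | 0.20 | 36% | 35% | 5.1% |
| 0.7 | 0.30 | 67% | 66% | 5.2% |
| 0.7 | 0.45 | 95% | 95% | 5.0% |

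**The reverse case.** With no direct effect and 0.45 SD of true modification, T2 − T0 is significant in 79% (r = 0.5) or 94% (r = 0.7). These are practically the same as the 78% and 95% when the whole 0.45 SD is direct, so the planned contrast does not tell the two apart. The T2 − T1 contrast does: 80% and 95% here, against 5% there.

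**Power of the T2 − T1 contrast for modest modification.** With 0.30 SD direct and 0.15 SD modification, T2 − T0 is significant in 80% or 95%. T2 − T1 is significant in only 15% or 23%. Formula check: 0.15/0.161 = 0.93 and 0.15/0.125 = 1.20, giving about 15% and 22%.

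**The case against.** The strongest reply is that the phase 2 test matches the formal objective. Objectives {7} and Trial design {8} claim superiority of one sequence over the other, and the planned comparison answers exactly that. This stands. For that hypothesis the percentages above are power against a real effect, not false-positive rates. A reader might infer that the phase 2 primary analysis is wrong; the document does not support that.

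A reader might also infer that every headache contrast runs from baseline to phase 2 or later, so that the direct effect is hidden. It is not. CALI-9 is measured at phase 1 post-treatment, and the discrete-time model yields a time-by-group term there.

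The synergy wording is hedged and sits in the abstract, Discussion, Limitations and Strengths. Limitations also concedes that later time points reflect CBT-Pain added to either phase 1 programme. Both points are fair, but the Discussion still ties synergy to this comparison, and the next sentence of Limitations gives synergy as the reason for the design. That is a mismatch between a stated inference and its stated test, not condensed detail.

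It is tempting to add that no analysis uses change in sleep as mediator or predictor. A journal article may leave that to the full protocol or SAP, so its absence is not counted here.

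Finally, a single high rejection rate would mislead. A baseline-adjusted test gives roughly 90% at r = 0.5 (SE = √(2 × 0.75/77) = 0.14; 0.45/0.14 = 3.2), but only if the full 0.45 SD arises in phase 1 and persists. The range is the honest summary.

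**Conclusion.** The concern holds for the interpretation, not for the primary test. The planned comparison estimates the total effect of placing CBT-I before CBT-Pain. It cannot by itself support statements about synergy or modified response, because the direct effect of CBT-I on headache, which Background {6a} leads one to expect, is part of it.

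With no modification, a persisting direct effect of 0.20 to 0.45 SD makes the change-from-baseline test significant in about 23% to 95% of trials, against about 5% for the contrast over the CBT-Pain period. The range rests on assumed alpha, correlations, direct effects and persistence. The algebra does not, although a direct effect that faded before phase 2 would contribute less.

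A reader might infer that the contrast over phase 2 would prove synergy. It would not. No arm receives CBT-I without CBT-Pain, and the abstract itself raises the possibility that pain improves only after sustained improvement in sleep. Such a delayed benefit would fall into that contrast too.

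**What to change.** 1. Keep the planned phase 2 CALI-9 comparison as the test of the combined sequence.
2. From the same mixed model, pre-specify as secondary the phase 2 time-by-group coefficient minus the phase 1 coefficient for CALI-9, with a confidence interval. Report it beside the phase 1 headache contrast, so that readers see both parts of the total.
3. Describe a positive baseline-to-phase 2 result as benefit of the combined sequence, not as synergy or improved response to CBT-Pain. Describe a positive phase 2-only contrast as consistent with improved response, stating that a delayed CBT-I benefit cannot be excluded.
4. Align the wording of the abstract, Discussion, Limitations and Strengths with the superiority objective.

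The cost is one linear contrast from a model already planned, and wording; no new data, arm or participants. The downside is power: about 15% to 23% for 0.15 SD of modification under the assumptions above. A null result must therefore not be read as evidence of no modification.

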**Methods:**

We will study a cohort of 180 adolescents, ages 11–17 years, with migraine (with or without aura, chronic migraine) and comorbid insomnia. In phase 1, youth will be randomly assigned to receive Internet-delivered CBT-I intervention or Internet sleep education control. In phase 2, all youth will receive Internet-delivered CBT-Pain intervention. Assessments will occur at baseline, immediately after phase 1 intervention, immediately after phase 2 intervention, and 6 months post-intervention. We will use a comprehensive multidimensional assessment of sleep and headache including self-report questionnaires, ambulatory actigraphy monitoring, and 14-day daily diaries.

**Discussion:**

Given the high prevalence of insomnia in adolescents with migraine, an extension of CBT-I intervention to this population will address an important gap in clinical practice and in conceptual understanding of the relationship between sleep and migraine. By testing a separate CBT-I intervention, we will be able to apply this treatment in the future to other pediatric populations (e.g., cancer, arthritis) who commonly experience comorbid insomnia.

**Trial registration:**

ClinicalTrials.gov NCT04936321. Registered on June 23, 2021.

## Administrative information

Note: The numbers in square brackets in this protocol refer to the SPIRIT checklist item numbers. The order of the items has been modified to group similar items (see http://www.equator-network.org/reporting-guidelines/spirit-2013-statement-defining-standard-protocol-items-for-clinical-trials/).

## Introduction

### Background and rationale {6a}

Migraine is a major pediatric health problem impacting 10–12% of adolescents [1, 2]. Poor sleep is a common comorbidity, with 60–70% of youth reporting elevated insomnia symptoms [3, 4]. Recent studies suggest 30% of adolescents with migraine meet the diagnostic criteria for insomnia [5]. Insomnia is associated with poor outcomes for youth with migraine including greater headache-related disability, more frequent headaches, higher pain intensity, greater depression/anxiety, and greater health service use [4, 6, 7]. There is robust evidence showing the efficacy of psychological treatment for improving headache-related disability and pain in youth with migraine [8, 9]. However, improvements in sleep have been inconsistent [10, 11]. In fact, our preliminary data show that poor baseline sleep is a risk factor for youth to achieve less improvement in pain outcomes with cognitive-behavioral pain treatment (CBT-Pain) [11].

To cope with migraine, youth commonly engage in maladaptive sleep behaviors (e.g., caffeine overuse, napping, excessive time in bed) that can increase negative cognitions about sleep, disrupt sleep physiology, and lead to a vicious cycle of insomnia symptoms that, in turn, increase the propensity for migraine [12, 13]. We propose that insomnia is a critical treatment target for youth with migraine and that treatment of insomnia could have positive effects on headaches by increasing healthy sleep behaviors and reducing anxiety at bedtime (see Fig. 1 for an illustration of this conceptual model).

**Fig. 1 Fig1:**
[figure not shown]
Cycle of migraine and insomnia is disrupted by CBT-I

Our research team developed a brief cognitive-behavioral treatment for youth with insomnia (CBT-I) delivered in person and demonstrated preliminary efficacy for improving insomnia, sleep quality, sleep hygiene, and sleep patterns in youth with migraine [14] and youth with general physical and psychiatric conditions [15]. Among youth with migraine, we also found improvements in headache-related disability and headache frequency [14]. Although youth and parents found CBT-I to be acceptable, a major barrier to treatment was the requirement of attending in-person treatment visits. Our research team has addressed this treatment barrier in other populations with chronic pain through the use of digital health interventions to deliver CBT-Pain [16, 17]. We expect that this approach will also be effective in delivering insomnia intervention to adolescents with migraine.

### Objectives {7}

The current randomized controlled trial explores the efficacy of Internet-delivered CBT-I intervention (called Firefly) for adolescents with migraine and co-morbid insomnia in a randomized controlled trial using two phases of treatment. In treatment phase 1, the effects of Firefly will be compared to Internet-delivered sleep education control (Sleep EDU) on insomnia symptoms (primary outcome) and sleep quality and sleep patterns (secondary outcomes). In treatment phase 2, both groups will receive Internet-delivered CBT-Pain intervention (called Web-based Management of Adolescent Pain (WebMAP)) to compare the effects of combined insomnia and pain intervention to sleep education and pain intervention on headache-related disability (primary outcome) and headache frequency, pain intensity, anxiety and depressive symptoms, and health-related quality of life (secondary outcomes).

### Trial design {8}

In this two-phase randomized controlled trial with two parallel study arms, we will assess the superiority of CBT-I over Sleep EDU and the superiority of the combined effect of CBT-I + CBT-Pain over Sleep EDU + CBT-Pain. The patient allocation ratio is 1:1. Outcome assessments are administered at baseline, phase 1 post-treatment, phase 2 post-treatment, and 6-month follow-up. See Fig. 2 for an illustration of the trial design and study flow.

**Fig. 2 Fig2:**
[figure not shown]
Trial design and study flow

## Methods: participants, interventions, and outcomes

### Study setting {9}

Participants will be referred to the study by providers in the Seattle Children’s Hospital Neurology Clinic. This is a tertiary care pediatric neurology clinic in an academic hospital that serves children and families from a 5-state region in the Pacific Northwest, USA.

### Eligibility criteria {10}

We will use a two-stage eligibility screening process. Providers in the Seattle Children’s Hospital Neurology Clinic will identify patients who are 11–17 years old with migraine and self-reported sleep difficulties. Providers will give families a study brochure and submit their contact information to the study team via a secure internal message in the hospital’s electronic health record after obtaining verbal permission to do so from the parent. After receiving referral information, the study staff will contact the families via telephone to conduct a second stage of eligibility screening with the adolescent and parent based on the criteria below. Eligibility criteria were informed by the American Headache Society (AHS) guidelines for trials of behavioral treatments for pediatric headache [18].

Adolescents must meet the following criteria to be eligible for enrollment:Age 11–17 years.Diagnosis of migraine with or without aura or chronic migraine without continuous headache, as defined by the International Classification of Headache Disorders 3rd Edition (ICHD-3) [19] by the referring provider in Neurology Clinic.Meets the research diagnostic criteria for insomnia disorder (self-reported sleep difficulties 3 or more nights during the past month with at least one daytime sleep-related problem) [20].Score on the Pediatric Migraine Disability Assessment scale (PedMIDAS) greater than 10, indicating at least mild headache-related disability [21].Headache frequency of 6 or more days per month [18].Access to the Internet on any web-enabled device.Adolescents on a stable dose (× 2 months) of prophylactic medications for migraine or sleep (antidepressants, anticonvulsants, supplements, etc.) will be eligible.

Adolescents who meet any of the following criteria will not be eligible for enrollment:Adolescent or parent cannot read in EnglishHas another primary sleep disorder (e.g., sleep apnea, narcolepsy) or an unusual sleep/wake schedule or circadian rhythm disorderIs currently experiencing a psychiatric crisis (e.g., active suicidality, psychosis)Received psychological therapy for insomnia or pain in the 6 months prior to screening

